## Methods/design

### Trial design

A multicentre three-arm RCT will be carried out to evaluate the efficacy and cost-effectiveness of adapted-NFPP compared with IY and TAU for preschool children with a research diagnosis of ADHD in a sample enriched to ensure a high percentage of potentially high-burden and difficult-to-treat cases. Participants will be randomly allocated to adapted-NFPP, IY and TAU in the ratio 3:3:1. Randomization will be stratified by participating centre and tranche.

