### Sample size

The trial is powered for two comparisons of interest.

Primary question: adapted-NFPP versus Incredible Years (Arm A vs Arm B).

Is adapted-NFPP superior to IY in terms of reductions in parent-rated ADHD symptoms? Assuming a conservative estimate of effect size difference of 0.4 standard deviation between adapted-NFPP and IY, an intraclass correlation of 0.08 for parents treated in the same IY groups and a drop-out rate of 10% (considerably higher than in the original trials) it is estimated that 141 individuals will be needed per treatment arm to provide sufficient power to test the hypothesis that the adapted-NFPP is superior to IY in terms of reduction in ADHD symptoms (total *N* = 282). This equates to a difference of mean 0.28 and standard deviation 0.7 on the SNAP-IV-P ADHD rating scale (the primary outcome) using a 5% two-tailed test of significance and 80% power. A design effect of 1.28 has been calculated from the formula:

$$1+\left(m-1\right)p$$

in the CONSORT (Consolidated Standards of Reporting Trials) statement for nonpharmacological interventions [66].

Secondary question: adapted-NFPP versus treatment as usual (Arm A vs Arm C).

Is the adapted-NFPP superior to TAU in terms of reductions in parent-rated ADHD symptoms? Again assuming a conservative estimate of effect size difference between adapted-NFPP vs TAU, a group of 141 adapted-NFPP and 47 TAU will give 81% power to detect an effect size of 0.5 on the SNAP-IV-P ADHD score (equating to a difference of mean 0.35 and standard deviation 0.7) with 5% two-tailed significance. No intraclass correlation has been applied for this calculation, as both adapted-NFPP and TAU will be delivered individually.

On this basis, each of the three centres will recruit approximately 110 families with a preschool-aged child (age 2 years 9 months to 4 years 6 months) with high levels of ADHD symptoms (total *n* = 329) into the trial. Families will be randomized with intention to treat to either (i) adapted-NFPP as an individually delivered, home-based parenting programme (*n* =141, leaving 127 for final analysis with 10% drop-out); (ii) IY delivered in groups of eight (*n* = 141, leaving 127 for final analysis with 10% drop-out); or (iii) TAU (*n* = 47, leaving 42 for the final analysis with 10% drop-out).

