### Statistical analysis

The main analyses will be performed using the intention-to-treat population. All results will be reported according to the CONSORT statement for nonpharmacological interventions [66]. The primary endpoint for the comparison between adapted-NFPP and IY will be the average ADHD score on items 1 to 18 of the SNAP-IV-P at post-treatment. The primary analysis of this endpoint will adjust for baseline SNAP-IV-P scores using a mixed-effect regression model [77] with treatment arm and time (pre- and post-treatment) as the fixed effects and therapist as a random effect. Subject to approval, this analysis will also include trial centre and recruitment tranche as randomization stratification factors. These models are especially valuable when used with longitudinal and trial data derived from parallel arms. A similar secondary analysis comparing adapted-NFPP and IY will be carried out 6 months after treatment. Secondary outcome measures, including the Child’s Solo Play Index, ECBI (Parent), ADHD SNAP-IV-T and SNAP-IV-T, together with SNAP-IV-P ODD scores, will be analyzed in the same way as SNAP-IV-P ADHD.

Subject to approval, a per-protocol analysis will also be performed. The parent will be considered to have completed the parenting programme if he or she had completed at least 8 of the 12 programme sessions. In the case of the IY programme, this will be either by attending the group or by receiving individual home-based sessions for any missed sessions.

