#### Therapist effects

Four or more therapists (depending on numbers recruited) will work in each of the three study centres with two therapists working on each intervention. The mixed effects regression models will include therapist as random effects within these models, allowing for the extent to which treatment effects differ between therapists and also accounting for the way in which participants are nested by therapist. Even when the difference between treatment effects can be assumed to be identical for all therapists, the mixed model can improve the precision of the treatment estimates by taking appropriate account of the different therapists in the analysis.

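### The primary model takes in the randomization strata only subject to an undefined approval; if centre were left out, its variance would go into the therapist effect and cost power

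*Protocol article*

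**What the plan says.** The Trial design section of the protocol article is unconditional: "Randomization will be stratified by participating centre and tranche". There are three centres, and the Recruitment section expects five or six tranches.

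The Statistical analysis section sets the primary comparison, adapted-NFPP versus IY on the post-treatment parent SNAP-IV ADHD score. The model adjusts for baseline score, has arm and time as fixed effects and has therapist as a random effect. It then adds: "Subject to approval, this analysis will also include trial centre and recruitment tranche as randomization stratification factors". Secondary outcomes are to be analysed in the same way.

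The Therapist effects section puts at least four therapists in each centre, "with two therapists working on each intervention". The Recruitment section has the two IY therapists leading a group together, while the two adapted-NFPP therapists work separately.

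**The concern.** Two primary models remain possible for one endpoint, and the one that stands without the approval ignores the factors used to randomize.

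This matters more than usual because therapist is nested in both centre and arm. With no centre term, a centre whose families score higher overall shows up as several high-scoring therapists. The model reads this as therapist variance and widens the standard error of the arm contrast. Yet both arms are present in every centre in equal proportion, so centre differences cancel from that contrast. The reported standard error would exceed the real sampling error, and a true difference could be missed.

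**Working it through.** **Inputs from the Sample size section.** "This equates to a difference of mean 0.28 and standard deviation 0.7 on the SNAP-IV-P ADHD rating scale", so d = 0.28/0.7 = 0.4; "using a 5% two-tailed test of significance and 80% power"; "an intraclass correlation of 0.08 for parents treated in the same IY groups"; "IY delivered in groups of eight"; "A design effect of 1.28 has been calculated from the formula"; 10% drop-out, 141 randomized and 127 analysed per arm.

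**The plan's own figure.**
- n per arm = 2 × (1.96 + 0.8416)² / 0.4² = 98.1, so 99.
- Design effect for groups of eight: 1 + 7 × 0.08 = 1.56. Averaged with 1.00 for the individually delivered arm, this is 1.28.
- 99 × 1.28 = 126.7, so 127 analysed; 126.7/0.9 = 140.8, so 141 randomized. The stated size reproduces.
- In SD units, the variance of the difference is V = 2 × 1.28/127 = 0.02016 and the SE is 0.142. Power = Φ(0.4/0.142 − 1.96) = 80.4%.

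**Omitting centre: approximation.** Let c be the centre share of total variance (assumed; the article gives none) and K the number of therapist clusters per arm. The true variance stays at V, but the model works with V + 2c/K. Power = Φ[(0.4 − 1.96 × √(V + 2c/K)) / √V]. With K = 6 (two therapists per arm in each of three centres):

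| c | model SE | power | loss (points, from unrounded values) |
|---|---|---|---|
| 0 | 0.142 | 80.4% | 0 |
| 0.01 | 0.153 | 75.9% | 4.6 |
| 0.02 | 0.164 | 71.1% | 9.3 |
| 0.03 | 0.174 | 66.3% | 14.2 |
| 0.05 | 0.192 | 56.7% | 23.8 |

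**Simulation, two therapists per arm per centre** (REML, z test, therapist ICC 0 to 0.05, 3,000 runs per cell). The loss is about 0 points at c = 0, 3 at 0.01, 5 at 0.02 and 11 to 15 at 0.05. This is below the approximation, because therapists who share a centre reveal only part of the centre variance.

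**Simulation, six adapted-NFPP therapists and three IY pairs** (IY group ICC 0.08, 7 completers per arm per centre-by-tranche cell, z test; 4,000 runs, last row 2,000):

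| centre / tranche share | power without strata | power with strata |
|---|---|---|
| 0 / 0 | 77.7% | 77.4% |
| 0 / 2% | 79.5% | 79.1% |
| 1% / 1% | 74.9% | 79.0% |
| 2% / 1% | 68.8% | 78.9% |
| 4% / 2% | 61.2% | 79.8% |
| 5% / 2% | 58% | 80% |

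The tranche-only row shows no loss. The simulated therapists work across tranches, so tranche variance does not enter the therapist component. With shares of 4% and 2%, null rejection was 2.8% without strata and 5.8% with them (2,000 runs).

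**Fewer clusters.** If each arm has only three clusters (one pair per centre), the simulated loss at c = 0.05 is 17 to 30 points with a z test.

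**Reference distribution.** With nine therapist clusters and a t test on cluster-level degrees of freedom (9 − 2 = 7 without strata, 9 − 4 = 5 with centre), power without and with strata is:
- 65.4% and 58.1% at 0 / 0
- 61.1% and 59.8% at 1% / 1%
- 54.6% and 58.6% at 2% / 1%
- 44.6% and 59.7% at 4% / 2%

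None of these simulations includes the baseline score as a covariate.

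**The case against.** The strongest reply is that inclusion is the plan. The sentence announces that the strata will be in the model, and the same kind of qualifier is attached to the per-protocol analysis and, under Trial status, to the end of recruitment. It reads most naturally as an amendment awaiting sign-off, which the full protocol or SAP may already have settled. This stands: omission is the fallback, not the design. The article still states its primary model conditionally, without saying who approves or when.

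A reader might go further and infer that the choice would be made after outcomes are seen. Nothing in the article suggests that.

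A reader might also attach one figure to the loss, for example the 18 to 19 points seen with centre and tranche shares of 4% and 2%. That figure rests entirely on variance shares the article does not give; its only ICC is for IY groups. Only a range with stated assumptions is defensible. Baseline adjustment would absorb part of any stable centre difference and reduce the loss.

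Finally, adding the strata is not free. If the arm effect is tested on therapist-level degrees of freedom, the centre terms use two of very few. With one pair per arm per centre, only 6 − 4 = 2 remain, and the adjusted model had lower power than the unadjusted one throughout. This also stands and belongs in the fix.

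**Conclusion.** The point holds as one of an unsettled primary model. The strata are unconditional in the randomization and conditional in the analysis, and the model that remains without them has too large a standard error for adapted-NFPP versus IY whenever centres differ.

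The cost is power only; the error is on the conservative side. With about six therapists per arm or the nine-cluster layout, a z test and no baseline covariate, the loss is 0 when centres do not differ and reaches at most about 20 to 24 points at an assumed 5% centre share. The two-therapist simulation gives 11 to 15 points there. Three clusters per arm would raise the loss, and baseline adjustment would lower it. The mechanism concerns centre; for tranche the effect is close to nil.

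The article does not support a claim that the trial plans to ignore its strata. The sentence also does not reach adapted-NFPP versus TAU: the primary model is specified only for adapted-NFPP versus IY.

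**What to change.** Remove the approval condition from the sentence on stratification factors. State centre and tranche as fixed effects in the primary adapted-NFPP versus IY model and in the secondary-outcome models that follow it. If the approval is a real requirement, name the body and complete it before any unblinded analysis.

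In the same edit, state how degrees of freedom for the arm effect are obtained. With few therapist clusters and a cluster-level t reference, the centre terms may bring no gain, or a loss, when centres hardly differ.

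The cost is a wording change plus the degrees of freedom: two for centre and four or five for tranche. The two for centre come from the therapist level if a cluster-level reference is used. No change to sample size or data collection is needed.

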#### Therapist effects

Four or more therapists (depending on numbers recruited) will work in each of the three study centres with two therapists working on each intervention. The mixed effects regression models will include therapist as random effects within these models, allowing for the extent to which treatment effects differ between therapists and also accounting for the way in which participants are nested by therapist. Even when the difference between treatment effects can be assumed to be identical for all therapists, the mixed model can improve the precision of the treatment estimates by taking appropriate account of the different therapists in the analysis.

#### Missing data

Drop-out in this trial is defined as noncompletion of measures at the end of the 12-week parenting programmes. A drop-out rate of 10% has been estimated and the rates of drop-out across the three arms will be compared using analysis of variance. The randomness of missing data resulting from drop-out will be explored across treatment arms and, if random, standard mixed-effect regression model procedures will be employed. If data loss is not random, the modelling strategy will be based on Yang and Shoptaw [78], which involves imputation of nonignorable missing data due to drop-out using different models. The effect of using several different models will be compared to estimate imputed values. This method allows an exploration of the range of possible effects of missingness and provides the most conservative estimate of treatment effects, taking into account missing data due to drop-outs.

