#### Cost-effectiveness analysis (CEA)

The aim of the CEA will be to determine whether the adapted-NFPP, a home-based parenting programme, is more cost-effective with children at high risk of poor outcomes than either a TAU group or a generic package (IY: active control).

In addition to cost per QALY (CUA), the within-trial CEA will also be estimated using the primary outcome measure SNAP-IV-P, looking at cost per unit change in the SNAP-IV-P score, to allow for the possibility that the EQ-5D is not sensitive to changes in ADHD symptoms.

The NICE [67] reviewed treatments for ADHD, and, in their economic evaluation, people with ADHD were either classified as responders or nonresponders, based on the Clinical Global Impression-Improvement (CGI-I) Scale. A study from Lloyd et al. [82] developed a classification system of four health states (normal; borderline to mildly ill; moderately to markedly ill and severely ill), reflecting different levels of severity of the patient’s symptoms. A similar approach will be explored, classifying children by severity using the primary outcome and the EQ-5D, depending on the variation in severity of those recruited. In addition, by mapping the severity scale to the improvement scale, the response to treatment will be estimated, to allow classification of children as responders or nonresponders, as described by NICE. Given that the adapted-NFPP has recently been adapted to address the specific needs of ‘hard-to-reach’ and ‘difficult-to-treat’ children, this analysis is appropriate. The results will be presented as point estimates and cost-effectiveness acceptability curves. Deterministic sensitivity analysis will be combined with probabilistic sensitivity analysis, to explore different types of uncertainty.

Missing data will be examined as to whether cases with missing data are similar to those with full economic data in a similar manner to the main trial analysis. If cases with missing data are similar to those with complete data, an analysis will be carried out using only cases with complete data (complete case analysis). If this is not the case, appropriate measures of imputing missing data, for example, multiple imputation, will be explored. This will be done in consultation with the trial statistician. If results using imputed values are produced, these will be in addition to those using a complete case analysis.

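### The missing-data rule lets a judgement that observed data cannot settle decide both the primary model and whether any nonignorable analysis is run

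*Protocol article*

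**What the plan says.** The Statistical analysis section of the protocol article names the primary analysis. It is a mixed-effect regression of the post-treatment parent-rated SNAP-IV ADHD score, with baseline adjustment, arm and time as fixed effects, and therapist as a random effect.

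The Missing data section then attaches a condition. It defines drop-out as not completing the measures at the end of the 12-week programmes, expects 10%, and compares drop-out rates across the three arms by analysis of variance. It continues: "The randomness of missing data resulting from drop-out will be explored across treatment arms and, if random, standard mixed-effect regression model procedures" are to be used. If the loss is judged not random, the strategy changes to imputation under several nonignorable models whose results are compared. The section says this approach explores a range of possible effects and "provides the most conservative estimate of treatment effects".

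No test or threshold is given for the judgement of randomness; only the comparison of rates has a named test. Nothing in the article plans the nonignorable models when drop-out is judged random.

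**The concern.** One judgement, made after the data are in, does two jobs. It selects the model that gives the primary estimate, and it decides whether robustness to informative drop-out is examined at all.

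The data cannot support that judgement. A drop-out has no post-treatment score by definition, so whether the loss depends on that score, given what was observed, cannot be seen. The rule can fail both ways:

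- **Judged random when it is not.** Outcome-dependent loss at similar rates in the two arms leaves nothing for the exploration to find, and the nonignorable models are not run.
- **Judged not random when the mixed model suffices.** Loss related only to arm or to baseline score may be called not random, although a likelihood-based mixed model that includes these variables handles it.

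At stake is whether a reader of the results can see how far the adapted-NFPP versus IY comparison depends on what is assumed about the families who left. Reasons for leaving could differ between one-to-one home sessions and a fixed-day group in a local hall, and parents who know their allocation rate the primary outcome. That the reasons do differ is an assumption, not something the article shows.

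**Working it through.** **1. The plan's own figure.** Inputs from the Sample size section: "using a 5% two-tailed test of significance and 80% power"; "difference of mean 0.28 and standard deviation 0.7 on the SNAP-IV-P ADHD rating scale"; "an intraclass correlation of 0.08 for parents treated in the same IY groups"; "A design effect of 1.28 has been calculated from the formula"; 10% drop-out.

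- n per arm = 2 × (1.960 + 0.842)² × 0.7² / 0.28² = 98.1, rounded up to 99.
- With the stated design effect: 99 × 1.28 = 126.7.
- With drop-out: 126.7 / 0.90 = 140.8, so 141 per arm.

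This matches the protocol. Nothing below changes it.

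**2. Bias that equal drop-out rates would hide.** Let d be the drop-out fraction in each arm, σ the SD, and k the amount, in SDs, by which an arm's drop-outs do worse than a missing-at-random model predicts. Then

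bias = d × σ × (k in one arm − k in the other).

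The article gives d = 0.10 and σ = 0.7. It gives no k, so the values below are assumptions, with k = 0 in the other arm.

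| k in one arm | Bias (SNAP-IV-P points) | Share of planned 0.28 |
|---|---|---|
| 0.25 | 0.10 × 0.7 × 0.25 = 0.0175 | 6% |
| 0.5 | 0.10 × 0.7 × 0.5 = 0.035 | 12.5% |
| 1.0 | 0.10 × 0.7 × 1.0 = 0.07 | 25% |

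If the departing arm is adapted-NFPP, its benefit is overstated; if it is IY, the benefit is understated. If k is the same in both arms, the bias is zero.

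**3. Can the exploration see it?** A simulation used 141 per arm, no true effect, SD 0.7 and 10% drop-out in both arms. Drop-out depended only on the part of the post-treatment score that baseline does not explain. Completers were compared with baseline adjustment. Assumptions not in the article: pre-post correlation 0.5, the strength of the drop-out mechanism (log-odds per SD), no clustering, and the form of the check. The check was taken as a 5% test of drop-out rates between the two main arms, with or without a 5% test of drop-outs against completers on baseline score.

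| Log-odds per SD (one arm, other arm) | Bias | Type I error | Rate check flags | Rate or baseline check flags |
|---|---|---|---|---|
| 0, 0 (purely random) | about 0 | 5.0% | 4.5% | 9.0% |
| 1, 1 (same mechanism) | about 0 | 5.7% | 4.6% | 9.3% |
| 1, 0 | 0.055 | 10.8% | 5.3% | 9.4% |
| 2, 0 | 0.087 | 21.7% | 4.4% | 9.1% |
| 1, −1 | 0.110 | 32.4% | 4.6% | 9.8% |

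The last two columns carry the point: at equal rates the check fires about as often under informative loss as under purely random loss. The type I errors belong to the missing-at-random comparison under those mechanisms. They do not measure harm done by the rule.

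**The case against.** The strongest reply is that the bias figures do not measure the cost of the rule. A missing-at-random primary analysis fixed in advance would carry the same bias, and no calculation here shows the nonignorable branch doing better as a primary analysis. That stands. The gain from a change is an unconditional sensitivity analysis, not a less biased primary estimate.

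Four stronger readings might be inferred, and the article does not support them:

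- **Informative drop-out always passes the check.** It can pass. If informative loss also makes the rates differ, the three-arm analysis of variance may react. With TAU at 10%, it rejects in about 15% of trials at 8% versus 12%, 20% at 10% versus 15%, 61% at 10% versus 20%, and 73% at 5% versus 15%. That detects unequal rates, which is a different question from whether the loss depends on the unseen score.
- **The primary analysis is unspecified.** The Statistical analysis section names a mixed model without condition. The trouble is that the Missing data section then makes its use conditional.
- **The economic analysis has the same fault.** The CEA section says "If cases with missing data are similar to those with complete data, an analysis will be carried out using only cases with complete data", and similarity on observed variables proves no more there. But any imputed results are to be reported in addition to complete cases, so the check does not swap one estimator for another.
- **The claim of a most conservative estimate is simply false.** The least favourable of several fitted models is the most conservative of those fitted, and what the cited method itself delivers cannot be checked here. What remains is that comparing models gives a range, and its direction depends on which arm's drop-outs did worse.

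A full analysis plan might add unconditional sensitivity analyses. The point concerns what this article states: a conditional rule that such a plan would have to override.

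**Conclusion.** The point holds in limited form. As written, the rule can skip the nonignorable analyses in the very situation they are meant for, and can move away from an adequate mixed model when the loss relates only to arm or baseline. That follows from how drop-out is defined and needs no numerical assumption.

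The size does rest on assumptions. At the planned 10% drop-out, with one arm departing by 0.25 to 1.0 SD, the unexamined bias is 0.0175 to 0.07 points against a planned 0.28; with a common mechanism it is about zero. This is a weakness to put right before analysis. It is not evidence that the trial's primary estimate will be wrong.

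**What to change.** Reword the Missing data section in three places:

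1. State that the mixed-effect model in the Statistical analysis section, with its baseline adjustment and therapist random effect, is the primary analysis under missing at random whatever the exploration shows. The comparison of drop-out across arms can stay as description.
2. Run the nonignorable models already planned in all cases, as sensitivity analyses, with drop-outs shifted separately by arm.
3. Replace the statement that the method "provides the most conservative estimate of treatment effects" with one saying that the range of estimates across these models will be reported.

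No change to the CEA rule is asked for. The cost is a few sentences and a few extra sensitivity runs; the 141 per main arm is unaffected.
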